# Oil-based versus water-based contrast media for hysterosalpingography in infertile women of advanced age, with ovulation disorders or a high risk for tubal pathology: study protocol of a randomized controlled trial (H2Oil2 study)

**DOI:** 10.1186/s12905-022-01707-z

**Published:** 2022-04-18

**Keywords:** Hysterosalpingography (HSG), Tubal patency testing, Cost–benefit analysis, Ethiodized oil, Infertility, Ongoing pregnancy, Oil-based contrast, Water-based contrast

## Abstract

**Background:**

In women with unexplained infertility, tubal flushing with oil-based contrast during hysterosalpingography (HSG) increases ongoing pregnancy and subsequent live birth rates when compared to tubal flushing with water-based contrast. It is currently unclear whether an HSG with oil-based contrast also results in more ongoing pregnancies and live births in women of advanced age, women with ovulation disorders, and women with potential tubal pathology when compared to an HSG with water-based contrast.

**Methods:**

We plan an international, multicentre, open-label, randomized controlled trial (RCT) studying three groups of infertile women who have an indication for tubal patency testing according to their treating physician and additionally; (1) are 39 years of age or older, (2) have an ovulation disorder or (3) have a high risk for tubal pathology based on their medical history. Women with an allergy for iodinated contrast medium are excluded, as are women with diabetes, hyperprolactinemia or untreated hyper- or hypothyroidism, and women with a partner with severe male infertility. After informed consent, women will be randomly allocated to the intervention, tubal flushing with the use of oil-based contrast during HSG or the control group, tubal flushing with the use of water-based contrast during HSG in a 1:1 ratio by the web-based system Castor. The primary endpoint will be ongoing pregnancy leading to live birth with conception within six months after randomization. Secondary outcomes are other pregnancy outcomes, used fertility treatments, adverse events and cost-effectiveness. Based on the expected ongoing pregnancy rate of 17% in the control group and 27% in the intervention group, the sample size will be 930 women (465 per group). Study inclusion is expected to be complete in four years.

**Discussion:**

This multicentre RCT will establish whether, for women of advanced age, women with ovulatory disease, and women who have a high risk for tubal pathology, there is a fertility enhancing effect of tubal flushing with oil-based contrast during HSG and whether the use of this contrast medium is cost-effective.

*Trial Registration* The study was prospectively registered in the Netherlands Trial Register on August 1st 2019 as ‘H2Oil2’ (reference number NL7925, https://www.trialregister.nl/trial/7925).

**Supplementary Information:**

The online version contains supplementary material available at 10.1186/s12905-022-01707-z.

## Background

Infertility, defined as the inability to conceive within 12 months of unprotected intercourse, was estimated to effect approximately 48.5 million couples worldwide in 2010 [1, 2]. Fertility work-up includes the medical investigation into the various causes of male and female infertility that have been identified. With male factor infertility referring to the (relative) absence of functioning spermatozoa, female infertility can refer to ovulation disorders, diminished ovarian reserve, tubal factor infertility, and uterine factor infertility [3]. Ovulation disorders can have various causes, of which polycystic ovary syndrome (PCOS) is the most prevalent [4]. Diminished ovarian reserve plays an increasing role in infertility as couples have been postponing their wish to conceive over recent decades [5]. Tubal factor infertility can be caused by current or past pelvic inflammatory disease such as an infection with *Chlamydia trachomatis*, previous pelvic surgery, peritonitis or endometriosis [6, 7]. Uterine factor infertility can consist of anatomical anomalies, such as congenital uterine anomalies, or intrauterine pathology such as polyps, myomas or adhesions [8]. In up to 30% of couples, the fertility work-up shows no abnormalities and this is classified as unexplained infertility [9, 10].

Part of the fertility work-up is assessing the risk for tubal pathology and if indicated, a tubal patency test can be performed. Hysterosalpingography (HSG) is traditionally used as first choice tubal patency test to rule out tubal pathology [3, 4]. Although HSG was initially introduced as a diagnostic test, therapeutic effects of tubal flushing, especially with oil-based contrast, have been studied extensively [11–14]. The most recent review [14] included six studies comparing HSG with oil-based contrast and water-based contrast. Three of these studies reported on live birth but meta-analysis could not be performed due to heterogeneity of the population.

The largest study among these randomized controlled trials is the H2Oil study [15]. This study was conducted to investigate the difference in ongoing pregnancy rates between tubal flushing during HSG with the use of oil-based and water-based contrast, in couples with unexplained or mild male infertility. This study excluded women aged 39 years or older, women with ovulation disorders, and women who had a high risk for tubal pathology. The H2Oil study showed a significant increase in ongoing pregnancies as well as live births within 6 months after HSG with oil-based contrast when compared to HSG with water-based contrast (relative risk (RR) 1.37, 95% confidence interval (CI) 1.16–1.61; P < 0.001 for ongoing pregnancy and RR 1.38, 95% CI 1.17 to 1.64; P < 0.001 for live birth) [15]. The long term follow-up of this study demonstrated that the fertility enhancing effect of oil-based contrast is still present five years after HSG (cumulative ongoing pregnancy rates 80.0% after oil-based contrast, 75.0% after water-based contrast, RR 1.07, 95% CI 1.00 to 1.14, cumulative live birth rates 74.8% after oil-based contrast, 67.3% after water-based contrast, RR 1.11; 95% CI 1.03 to 1.20) [16]. This study additionally demonstrated that HSG with oil-based contrast leads to a significantly shorter time-to-pregnancy compared to HSG with water-based contrast (10.0 vs 13.7 months; hazard ratio 1.25; 95% CI 10.9 to 1.43). Robust studies investigating the fertility enhancing effect of oil-based contrast during HSG in women who were 39 years of age or older, women with ovulation disorders, and women who have a high risk for tubal pathology are lacking.

In the current socio-economic climate, where health care costs are increasing and the importance of evidence-based health care is underlined, the results of previously mentioned studies among couples with unexplained infertility cannot be extrapolated to couples with other types of infertility and therefore separate evaluation is needed.

This randomized controlled trial aims to investigate the effectiveness and cost-effectiveness of the use of oil-based versus water-based contrast during HSG, in women with previously unevaluated causes of infertility: women who are 39 years of age or older, women with ovulation disorders, and women who have a high risk for tubal pathology.

## Methods

This international, multicentre, randomized controlled trial will be performed in university, teaching and non-teaching hospitals in the Netherlands and the United Kingdom. A list of currently participating hospitals is available as Additional file 2*.* The trial has obtained ethical approval by the Institutional Review Board (IRB) of the Amsterdam UMC location Vrije Universiteit (registration number 2018.289), the Research Ethics Committee London Harrow (20/LO/0607), and the board of directors of all participating centres.

### Participants

Women who are scheduled for an HSG as part of their fertility work-up can participate if they meet at least one of the following criteria: (1) women who are 39 years of age or older, (2) women who have an ovulation disorder (ovulation disorders will be defined as less than eight menstrual cycles per year), or (3) have a high risk for tubal pathology (high risk will be defined as a past chlamydia infection, pelvic inflammatory disease, peritonitis, known endometriosis and/or pelvic surgery including tubectomy for ectopic pregnancy). In order to ensure adequate sample sizes in all three groups of participants, women meeting more than one criterion will be included according to the criterion that comes first in ranking. The ranking is based on the expected prevalence of the three subgroups of women within the study population, with the lowest expected prevalence highest in ranking. Women will be excluded if they have an endocrine disorder known to decrease natural pregnancy chances (e.g. diabetes, unregulated hypothyroidism or hyperthyroidism), iodine contrast medium allergy or a male partner with severe infertility (a pre-washed total motile sperm count below three million sperm per millilitre).

### Randomization and blinding

Infertile couples will be screened in the outpatient clinic by their attending physician. Eligible women will be informed by a dedicated research nurse or physician in their centre. Women who give written consent will be randomized for HSG with oil-based contrast (intervention group) or with water-based contrast (control group) in a 1:1 ratio, using a permuted block design with block sizes varying from 4–8 cases. Randomization will be performed using the web-based program Castor EDC (Castor Electronic Data Capture, Ciwit BV, Amsterdam, the Netherlands), and stratified according to centres and by infertility diagnosis (age 39 years or older, ovulation disorder, and high risk for tubal pathology). The trial is not blinded with respect to participants and health care professionals since the allocation will be evident in further fertility workup. Oil-based contrast has a higher iodine concentration than water-based contrast and together with its hydrophobic qualities this makes oil-based contrast easily distinguishable from water-based contrast on X-ray or fluoroscopy images [17]. The primary outcome is objective, and therefore we do not expect that lack of blinding will influence the findings.

### Intervention

The HSG procedure will be performed after cessation of menstrual bleeding or after progesterone-induced vaginal bleeding in case of anovulation. With use of a cervical vacuum cup, a metal cannula (hysterophore), an acorn cannula or an HSG balloon catheter, the iodinated oil- or water-based contrast medium will be infused into the uterine cavity and several radiographs will be taken to visualize the uterine cavity and Fallopian tubes according to local protocols. The procedure will be discontinued if signs of intravasation are visible on the radiographs, as intravasation of specifically oil-based contrast might lead to oil-embolisms, a known and potentially dangerous complication [18]. The results of the HSG will describe whether the Fallopian tubes are patent and whether there are any visual abnormalities in the cervix, uterine cavity, Fallopian tubes or peritoneal cavity. In the intervention arm, the HSG will be performed with a maximum of 15 millilitre of oil-based contrast (Lipiodol Ultra Fluid®, Guerbet, Villepinte, France) to minimize the chance of (temporary) hypo- or hyperthyroidism [18]. In the comparator arm, the HSG will be performed with water-based contrast medium (iodixanol, Visipaque®, General Electric Healthcare, Buc, France), for which no maximum dosage is advised. The batch number and expiration date of the used flasks of contrast medium will be reported for the purpose of drug accountability.

Pre- and post-HSG use of analgesics and antibiotics, and subsequent management will be performed according to local protocol. Women will receive the adjusted Amsterdam Preoperative Anxiety and Information Scale (APAIS) questionnaire prior to their HSG procedure to score their anxiety score prior to HSG and to be able to relate this to their pain level during HSG [19]. Immediately after the procedure they will be asked to score their pain using a Visual Analogous Scale (VAS) ruler (ranging from 0 to 10 cm).

The choice of fertility treatments will be based on the results of the fertility work-up (including the outcome of the HSG) according to the Dutch fertility Guideline or the Clinical guideline by the National Institute for Healthcare and Excellence (NICE) [4, 20–22]. Anovulatory women will be offered ovulation induction, and women aged 39 years or older may be offered Intra Uterine Insemination (IUI) or In Vitro Fertilization (IVF). In case of suspected uni- or bilateral tubal pathology, women can be scheduled for IVF or a diagnostic or therapeutic laparoscopy followed by IVF if bilateral tubal occlusion is confirmed, according to the local protocol of the participating centres. Women with a high risk for tubal pathology, but without tubal pathology at HSG or laparoscopy, and with a regular menstrual cycle who are below 39 years of age will be advised expectant management or IUI, guided by their calculated prognosis for natural conception using the model of Hunault or other local protocols [23]. For women aged 39 or over, the Hunault prognostic model is not verified and these women will often be advised IUI or IVF immediately.

As the compared strategies (HSG with oil-based contrast versus HSG with water-based contrast) are already applied in current practice, no additional risks or burdens are expected for participating women.

### Outcomes

The primary outcome of this trial is ongoing pregnancy leading to live birth, with conception within six months after randomization. Ongoing pregnancy will be defined as an intrauterine pregnancy with heartbeat on ultrasound examination at twelve weeks of gestation, live birth as a live born neonate beyond 24 weeks of gestation. Secondary outcomes will include clinical pregnancy (ultrasound confirmed intrauterine gestational sac), ongoing pregnancy, miscarriage (loss of clinical or ongoing pregnancy or diagnosis of a pregnancy without positive foetal heartbeat before twelve weeks gestation), ectopic pregnancy (ultrasound or surgically confirmed extra-uterine pregnancy). Pregnancy complications, complications of HSG such as intravasation, infection and hypo- or hyperthyroidism, and a cost-effectiveness analysis will also be part of the secondary outcomes. Our hypothesis is that HSG with oil-based contrast will increase ongoing pregnancy rates and will reduce time to ongoing pregnancy in all three subgroups, thereby reducing the need for assisted reproductive technology (ART) and thus lowering the costs. In addition, we will study the procedural discomfort or pain and relate this to pre-procedural anxiety, using a modified APAIS questionnaire [19].

### Follow-up

Data on fertility treatments and pregnancy outcomes will be collected until six months after randomization in a structured electronic case report form using Castor EDC. If a pregnancy occurs within six months, the outcome of the pregnancy will be followed. If the necessary information cannot be extracted from the medical record, women will receive a digital questionnaire about treatment and pregnancy outcomes or they will be contacted by a dedicated researcher to conduct the follow-up questionnaire by phone. All participating women will receive a digital questionnaire on productivity-loss and health care costs (iPCQ) six months after randomization (see Table 1) [24].

**Table 1 Tab1:** SPIRIT figure

Time-point	Study period				
	Enrollment	Allocation	Post-allocation		
	t−1	t0	t1	t2	t3
Enrollment					
Eligibility screen	X				
Informed consent	X				
Allocation		X			
Interventions					
HSG with oil-based contrast			X		
HSG with water-based contrast			X		
Assessments					
Demographics		X			
APAIS			X		
Pain score (VAS)			X		
HSG procedure and results			X		
Adverse effects			X		
iPCQ				X	
Treatments				X	
Pregnancies				X	
Pregnancy follow-up					X

t−1: Prior to inclusion; t0: Study inclusion; t1: HSG procedure, usually within 4 weeks of inclusion (t0); t2: end of initial follow-up 6 months after randomization; t3: pregnancy follow-up, at last 9 months after t2

### Sample size

Our hypothesis is that HSG with oil-based contrast will increase the live birth rate with 10% in three infertility groups: (1) women aged 39 years or older, (2) women with ovulation disorders and (3) women who have a high risk for tubal pathology. To detect an increase of 10% in live birth rate from 17 to 27%, 395 women per group are needed (alpha 1%, beta 20%, Z-test with unpooled variances as calculated in PASS 2020). Anticipating a loss to follow-up rate of 15%, the total number of participants required is 930 (465 in each arm of the trial). With this number we have 80% power to study the 10% difference in live birth rate in the intervention versus control group in the stratified design using Cochrane-Mantel-Haenzel.

### Statistical analysis

Categorical data will be reported as absolute numbers and percentages. Normally distributed continuous variables will be summarized as means with standard deviations, and non-normally distributed continuous variables will be reported as medians with interquartile ranges. The primary analyses will done according to the intention to treat (ITT) principle, including all randomised women. Differences in live births will be expressed as crude and stratification adjusted risk ratio and absolute risk difference with associated 95% and 99% confidence intervals (CI) using log-linear binomial regression. We will construct Kaplan–Meier curves, estimating the cumulative probability of conception leading to live birth over time and use the log-rank test to assess differences. Additionally, we will do a cox proportional hazard analysis to evaluate the difference in primary outcomes over time while accounting for the subgroups and evaluating presence of interaction. Continuous outcomes will be measured at multiple time-points and will be analysed with the use of linear mixed models. We will subsequently compare intervention and control treatment within the stratified groups (1) women aged 39 years or older, (2) women with ovulation disorders and (3) women who have a high risk for tubal pathology. Women meeting more than one criterion will be included in the group that comes first in ranking as described earlier. Within these stratified groups pregnancy outcomes will be expressed as risk ratio, risk difference and hazard ratio with 95% CI.

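### The log-rank test for the conception curves is named without the diagnosis strata used in randomisation; a minor loss, confined to a supportive test

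*Protocol article*

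**What the plan says.** - **Design.** Under Randomization and blinding, allocation is "in a 1:1 ratio, using a permuted block design with block sizes varying from 4–8 cases", and it is "stratified according to centres and by infertility diagnosis". Diagnosis has three levels: age 39 or over, ovulation disorder, and high risk of tubal pathology.
- **Power.** Under Sample size, the calculation uses "alpha 1%, beta 20%, Z-test with unpooled variances as calculated in PASS 2020". The closing power statement concerns the live-birth difference "in the stratified design using Cochrane-Mantel-Haenzel".
- **Binary analysis.** Under Statistical analysis, the live-birth risk ratio and risk difference are given both crude and adjusted for stratification.
- **Time to event.** The same section plans Kaplan-Meier curves and will "use the log-rank test to assess differences". It then adds a "cox proportional hazard analysis to evaluate the difference in primary outcomes over time while accounting for the subgroups", which also looks at interaction, and hazard ratios within each diagnosis group.

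The log-rank sentence is the only one of these between-arm comparisons that says nothing about strata.

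**The concern.** The section mentions adjustment where it intends it, in the sentences on either side of the log-rank test. The natural reading of the bare term is therefore the ordinary unstratified test.

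The diagnosis groups are unlikely to share one conception rate. The Intervention section sends them down different routes: ovulation induction for anovulatory women, often immediate insemination or IVF advice from age 39, and expectant management or insemination for women under 39 with regular cycles and no tubal pathology found. When allocation is balanced within prognostic groups and the test ignores those groups, its variance is slightly too large for the design. The test then rejects a little too seldom and can lose power.

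At stake is the p-value attached to the conception curves. It could be weaker than the design allows, and out of step with the diagnosis-adjusted hazard ratio reported beside it. Shorter time to ongoing pregnancy is part of the hypothesis in the Outcomes section, so readers will look at that p-value.

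**Working it through.** **1. The plan's own figure.** Inputs from Sample size: 17% against 27%, alpha 1%, power 80%, unpooled variances. The article does not state sidedness; two-sided reproduces its number.

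n = (z₀.₉₉₅ + z₀.₈₀)² × [p₁(1−p₁) + p₂(1−p₂)] / (p₁−p₂)²
= (2.576 + 0.842)² × (0.1411 + 0.1971) / 0.10² = 394.98, so 395 per arm.

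395 / 0.85 = 464.7, so 465 per arm and 930 in total. The stated size reproduces exactly, and it belongs to the binary outcome.

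**2. The same inputs for a log-rank test.** With constant hazards, HR = ln(0.73)/ln(0.83) = 1.69. Expected events: 395 × (0.17 + 0.27) = 173.8. Schoenfeld power = Φ(√(173.8/4) × ln 1.69 − 2.576) = Φ(0.88) = 81.0%. This is the benchmark when all groups share one rate.

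**3. Power with and without strata, common hazard ratio.** Simulation: 395 per arm, HR 1.69, exponential times cut at 6 months, blocks of 4, 6 or 8, two-sided 1%, 1,500 runs. Assumed, because the article does not give them: control rates by diagnosis (averaging 17%), equal group sizes, 30 centres, and a centre SD of 0 or 0.3 on the log hazard.

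| Control rates | Centre SD | Plain | By diagnosis | Diagnosis × centre |
|---|---|---|---|---|
| 17/17/17% | 0 | 80.1% | 80.3% | 79.3% |
| 17/17/17% | 0.3 | 80.5% | 80.3% | 80.0% |
| 12/17/22% | 0 | 79.6% | 80.2% | 78.9% |
| 12/17/22% | 0.3 | 80.5% | 81.2% | 80.1% |
| 10/16/25% | 0 | 77.2% | 78.7% | 77.2% |
| 10/16/25% | 0.3 | 79.0% | 80.7% | 79.2% |
| 5/16/30% | 0 | 75.7% | 79.2% | 78.6% |
| 5/16/30% | 0.3 | 73.1% | 79.1% | 77.8% |

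The Monte Carlo standard error is about 1 point per entry. The tests were compared on the same data, so differences are more precise. Stratifying by diagnosis changes power by −0.2 to +1.7 points for equal to moderate spread and by +3.5 to +6.0 points for the sixfold spread. Crossing with centre gives about −1 to +0.2 points in the first three settings. The reason is sparse cells: 790 women over 90 cells is about 9 women and 174/90 ≈ 2 events per cell.

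**4. Dependence on the effect scale.** A second simulation (4,000 runs, three equal groups, no centre effect):

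| Control rates | Effect in every group | Plain | By diagnosis |
|---|---|---|---|
| equal | risk ratio 27/17 | 79.8% | 79.8% |
| 10/25/16% | risk ratio 27/17 | 81.0% | 82.7% |
| 6/30/15% | risk ratio 27/17 | 81.9% | 86.3% |
| 10/25/16% | +10 points | 79.7% | 79.5% |
| 6/30/15% | +10 points | 80.6% | 80.2% |

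With unequal group sizes (assumed 15/25/60%) and +10 points, the results were 80.1% against 79.9% and 79.6% against 79.6%. The gain vanishes on the absolute scale because the hazard ratios then differ: 6 to 16% is ln(0.84)/ln(0.94) = 2.82, while 30 to 40% is ln(0.60)/ln(0.70) = 1.43. The stratified test is at its best when the hazard ratio is common.

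**5. Error level under no effect.** At nominal 1%, the plain test rejected in 0.87% of 20,000 runs (standard error √(0.01 × 0.99/20,000) = 0.07 points, so under two standard errors from nominal) and in 0.80% in a separate run at wide spread. At 5/16/30% its Z statistic had SD 0.95 to 0.97 and it rejected about 3.9% at nominal 5%. For equal to moderate spread the SD was 0.98 to 1.03, with no clear conservatism.

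**The case against.** Several points tell against making much of this, and most of them stand.

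- **The article does not say that the test is unstratified.** The strata may be set out in an analysis plan that is not shown. This limits the point to the wording as it stands. It does not remove it, because the same paragraph names strata for the analyses around this one.
- **The time-to-event comparison is already adjusted.** A reader might infer that the whole comparison of time to conception ignores the strata. It does not: the next sentence plans a Cox model that accounts for diagnosis, and hazard ratios follow within each group. Only the log-rank test is at issue.
- **Crude beside adjusted is a deliberate pattern.** The risk ratio is reported both ways, and a stratified test does not test the pooled curves exactly as drawn. That is fair for description. It is a weaker argument for the only test named for the curves, since the crude risk ratio has a stated adjusted counterpart and the log-rank test has none.
- **The loss depends on assumptions.** The Sample size section hypothesises a 10% rise, from 17 to 27%, in the three groups. Read as 10 points in each group, it leaves nothing to gain. This stands in full. But stratifying by diagnosis cost at most about 0.4 points in any setting tried, so the change carries little risk.

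**Conclusion.** The point holds as a minor one. A plain log-rank test does not match the stratified design. If baseline conception rates differ between diagnosis groups, it is slightly conservative. Under a common relative effect it gives up about 0 to 2 points of power at equal to moderate spread and about 4 points at wide spread (3.5 to 6.0 across the runs). With equal rates or a constant 10-point difference it gives up nothing. These sizes rest on assumed group rates and constant hazards; group sizes, centre number and centre variation were also assumed.

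Two stronger readings are tempting and unsupported. One is that the primary conclusion or the stated 80% power is weakened. Both belong to the live-birth comparison, which is stratification adjusted and whose sample size reproduces. The other is that the trial loses control of its error level. Any departure is towards too few rejections, is clear only at the wide spread, and adds no false positives.

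**What to change.** In the Statistical analysis section, replace the plain log-rank test with one stratified by the three infertility diagnosis groups, and fit the overall Cox model for the treatment effect with the same diagnosis strata. Test and hazard ratio then share one structure. The interaction between treatment and diagnosis can still be examined in that model. Do not cross diagnosis with all centres in these strata: with many small cells the gain can disappear.

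The cost is one line of wording, settled before outcome data are seen by arm. It needs no further data or participants and leaves the sample size as it is.
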